### ***MRI Interpretation***

MRI interpretation is centralized to Capio St Görans hospital. Assessments are based on “Assessment Without Adequate DCE” from PI-RADS v2 and v2.1.

[name] [name] is responsible for MRI interpretation. [name] or 1-2 other, experienced radiologists at his department performs all MRI interpretations.

### ***Fusion biopsy technology***

#### ***Brand/models***

#### ***BK Medical (BK Ultrasound ; [www.bkultrasound.com/bk-medical/fusion](http://www.bkultrasound.com/bk-medical/fusion))***

The BK Medical fusion system is the only fusion device compatible with BK Medicals ultrasound devices, used by the urology departments participating in the study. The system represents a second generation ultrasound system with integrated MRI Fusion. MRI data is imported through HIPAA-compliant PACS connection with the local radiology department.

#### ***Definition of targeted biopsies***

Using MRI data with pre-marked borders of the prostate and tumor, fusion of MRI images and ultrasound images are performed bedside. Using local anesthetic and antibiotic prophylaxis, lesions are according to below. Targeted biopsies are always combined with systematic biopsies.

#### ***Biopsy procedure for targeted biopsies***

**PI-RADS≥3:** 3-4 targeted biopsies on marked lesions + systematic biopsies

**Large diffuse lesions or poor image quality:** Systematic biopsies including lesion

**No PI-RADS $\geq$ 3, diffuse lesions and at least acceptable image quality:** No biopsies are performed.

### ***Definition of systematic biopsies***

10-12 systematic biopsies are taken from the peripheral zone as previously described in STLHLM3 and the National Guidelines. Extra biopsies are allowed from additional sites visible on ultrasound or according to palpatory findings. In summary, systematic biopsies are performed in the peripheral zone as 4 lateral and para-median biopsies on the left and right side, in the base and mid part of the gland. In the apical third of the gland one lateral left and right biopsy is performed.

### ***Pathology***

Pathology is centralized to Unilabs/Capio St Görans hospital. [name] is responsible for the integrity of analyzes of pathological specimen. 2-3 uro-pathologists at dr [name] department assesses all pathological specimen with intermittent cross-validation between them. Pathology preparation and reporting follow ISUP 2014 guidelines.

The pathology preparation is done by Unilabs as part of the normal clinical routine. Biopsy specimens are analyzed according to local practice.

Localisation of biopsies in the prostate are described using Swedish National Guideline nomenclature (A1-4; B1-4; C1-4; anterior/posterior). Gleason Score, mm cancer and % Gleason 4 is reported on each needle specimen.

Pathologist notes results in the usual way in the laboratory system. The result of the pathological analysis is submitted in accordance to existing clinical routines to the referring urologist. A copy of the result is delivered to the study administration.

## **13.5. Outcomes**

Primary outcome:

1. Diagnosed ISUP grade  $\geq$  2 cancers

Key secondary outcomes:

2. Diagnosed ISUP grade 1 cancers
3. Performed biopsies
4. Performed MRI examinations

See statistical analysis plan (SAP) for details.

### ***Additional endpoints***

We are collecting data on a large number of endpoints in the study. See SAP for detailed information regarding the definition of these endpoints.

### ***13.6. Follow-up***

All participants were followed a minimum of 200 days after receiving blood test results. Main study outcomes are assessed after prostate biopsy procedures (plus 30 days of follow-up for post-biopsy infections). Additional participant data will be secured in the following circumstances:

#### ***No suspicious lesion on MRI:***

Men in the experimental arm without suspicious lesions on MRI will be informed and recommended follow-up by the responsible, local urologist. After additional ethical application, the co-investigators might initiate retrospective follow-up of these participants.

#### ***Men with diagnosed prostate cancer***

Participants with prostate cancer diagnosed on biopsy within the study will be followed up after the biopsy to secure data on the following: Treatment modality (Active Surveillance, Surgery, Radiation); Treatment lead-time and site; Pathological report after surgery (positive margins, T-stage, etc). Data will be assessed through medical records intermittently.

### ***13.7. Serious adverse events***

Study nurse will monitor serious adverse events after the prostate biopsy procedures (up to 30 days post biopsy). To ensure this, the study nurse will check medical journals for hospitalization within 1 week after the biopsy procedure in the journal systems Take Care and Cosmic (covering the main part of hospitals in Stockholm region). This will be initiated as individual biopsy results are registered at the study administration. Results will be provided to the Data Safety and Monitoring Board.

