### Key secondary aims

1. To test whether targeted prostate and systematic biopsies performed in MRI positive men will lead to: non-inferior sensitivity for detecting clinically significant cancer (ISUP grade group  $\geq 2$ ); reduced number of performed biopsy procedures; and lower proportion of men with elevated risk who experience severe post-biopsy infections compared to systematic biopsies for men with elevated risk (defined as being positive on PSA and/or Stockholm3) of prostate cancer in prostate cancer screening.
2. To test whether targeted prostate biopsies performed in MRI positive men will lead to: non-inferior sensitivity for detecting clinically significant cancer (ISUP grade  $\geq 2$ ); reduced number of performed biopsy procedures; and lower proportion of men with elevated risk who experience severe post-biopsy infections compared to systematic biopsies for men with elevated risk (defined as being positive on PSA and/or Stockholm3) of prostate cancer in prostate cancer screening.
3. To test whether a diagnostic chain consisting of Stockholm3 followed by MRI and targeted+systematic biopsies versus a diagnostic chain based on PSA  $\geq 3$  ng/ml followed by MRI and targeted+systematic biopsies will lead to: non-inferior sensitivity for detecting clinically significant cancer (ISUP grade group  $\geq 2$ ); an inferior sensitivity for ISUP1 cancers (i.e. reduced overdiagnosis); and a reduction in the number of MRI examinations and performed biopsies.
4. To test whether a diagnostic pathway using the Stockholm3 test to select men for further workup using MRI followed by ONLY targeted biopsies (S3M+MRI+TBx) has non-inferior sensitivity for detecting clinically significant cancer (ISUP grade  $\geq 2$ ) and reduces the number of performed biopsy procedures compared with a diagnostic pathway using systematic biopsies in men with PSA  $\geq 3$  ng/mL (PSA+SBx).

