| Maximum GS $\geq 4$ cancer core length | mm      | maximum length of Gleason $\geq 4$ cancer in any core                                                                                                                                       |
| Serious adverse events                 | Yes/No  | (1) Hospitalisation within 30 days after biopsy procedure, (2) infection treated with antibiotics within 30 days after biopsy procedure, or (3) death within 30 days after biopsy procedure |

*Independent variables*

| Variable                          | Measure | Comment                                        |
|-----------------------------------|---------|------------------------------------------------|
| Age                               | Years   | At referral creation                           |
| Previous prostate biopsy          | Yes/No  | Patient self-reported                          |
| Family history of prostate cancer | Yes/No  | Any first degree relative with prostate cancer |
| PSA                               | ng/ml   | At blood test                                  |
| free PSA                          | ng/ml   | At blood test                                  |

|                       |                         |                       |
|-----------------------|-------------------------|-----------------------|
| Stockholm3 risk score | % risk of ISUP $\geq$ 2 | At blood test         |
| prostate volume       | ml                      | MRI defined           |
| PI-RADS               | 1–5 (integer)           | Maximum PI-RADS score |

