## Statistical analysis

All analyses will be performed after the study is completed and the database is released. All statistics, including tables, figures and listings, will be performed using R version >3.5. Men creating referral before 2020-01-09 are included in main analysis. All participants with will be followed a minimum of 200 days after receiving the result from their blood sample (PSA and Stockholm3 score). In addition, biopsied men will be followed at least 30 days post-biopsy to monitor adverse events, and participants undergoing radical prostatectomy prior to database lock will be followed until pathology results from the prostatectomy are available.

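### Protocol 13.7 commits to 30 days of safety monitoring, but the only check it describes looks for hospitalisation in the first week, which does not match the SAP's three-part 30-day endpoint

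*Combined protocol and SAP*

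**What the plan says.** Protocol 13.7 opens with a 30-day commitment: "Study nurse will monitor serious adverse events after the prostate biopsy procedures (up to 30 days post biopsy". The sentence that explains how this is secured gives a shorter window and a single event type: "the study nurse will check medical journals for hospitalization within 1 week after the biopsy procedure". The check starts when a man's biopsy result is registered with the study administration. It uses two record systems described as "covering the main part of hospitals in Stockholm region", and its results go to the DSMB.

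The SAP table of other secondary endpoints defines a serious adverse event by three components. The first is "1) Hospitalisation within 30 days after biopsy procedure", the second is "infection treated with antibiotics within 30 days after biopsy procedure", and the third is death in the same 30 days. The second component does not require admission.

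Two further places use 30 days. Protocol 13.6 adds 30 days of follow-up for infections after biopsy, and the SAP section on statistical analysis says that "biopsied men will be followed at least 30 days post-biopsy to monitor adverse events".

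On use of the data, the SAP section on secondary endpoints plans to report the proportion of men with these events by arm. Key secondary aims 1 and 2 include a "lower proportion of men with elevated risk who experience severe post-biopsy infections".

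**The concern.** Three statements promise 30 days, and the one sentence that says what will be done covers a week. A nurse who follows protocol 13.7 literally has no instruction to look for an admission on day 12, for an infection treated outside hospital, or for a death that did not follow a first-week admission. If a man with nothing found in week 1 is then entered as event-free for the 30-day endpoint, harm is understated.

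The trial argues that MRI selection spares men biopsies and so spares them infections. The safety comparison by arm is the evidence for that part of the argument, and the same counts inform the DSMB.

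**Working it through.** **Step 1. Set the check against the endpoint.**

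| SAP component | SAP window | Covered by the check in protocol 13.7 |
|---|---|---|
| Hospitalisation | 30 days | First week only, in most hospitals of the region |
| Infection treated with antibiotics | 30 days | Only if it leads to a first-week admission |
| Death | 30 days | Only if it shows in the record of a first-week admission |

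Days with no described ascertainment: 30 − 7 = 23, and 23/30 = 77% of the window. Components directly sought: 1 of 3.

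**Step 2. Try the other reading of the sentence.** The week could describe when the check is made, not when the event occurs. A check completed by day 7 still cannot see days 8–30, and a search for hospitalisation still does not find infections treated outside hospital. The gap remains under both readings.

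**Step 3. Look for another procedure.** Protocol 13.6 and the SAP section on statistical analysis state a follow-up period but no method. The primary data sources in protocol 14.1 are laboratory referrals, biopsy referrals and reports, pathology, MRI and blood results; none is an adverse-event source. The documents describe no later record check, patient contact, prescription source or death register.

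**Step 4. Scale (illustration only).** The plan gives no expected number of adverse events, so there is no figure to reproduce. Inputs:

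- about 1,700 men completing work-up (SAP, updated sample size);
- 2:3 allocation (protocol 13.3);
- 55% MRI-negative (protocol addendum), so 45% of the experimental arm biopsied;
- 1–2% severe infection per biopsy (protocol 8.3);
- a capture fraction *c*, which the documents do not give and which is assumed here at 1, 0.75 and 0.5.

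Control arm: 1,700 × 2/5 = 680 men, all biopsied. Experimental arm: 1,700 × 3/5 = 1,020 men, of whom 1,020 × 0.45 = 459 are biopsied. The 459 is slightly low, because MRI-negative men with Stockholm3 ≥ 25% are also biopsied.

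Expected events = men biopsied × rate × *c*. The absolute difference is per man in the arm: rate × *c* × (1 − 0.45).

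| *c* | Control events | Experimental events | Difference, percentage points |
|---|---|---|---|
| 1 | 6.8–13.6 | 4.6–9.2 | 0.55–1.10 |
| 0.75 | 5.1–10.2 | 3.4–6.9 | 0.41–0.82 |
| 0.5 | 3.4–6.8 | 2.3–4.6 | 0.27–0.55 |

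The ratio of the two proportions is 0.45 in every row. Equal loss in both arms leaves the ratio alone and shrinks the counts and the difference. If the difference were tested (one-sided 0.025, pooled variance), power would be about 0.29–0.49 at *c* = 1 and 0.18–0.29 at *c* = 0.5. The rate used is for severe infection, so these are not expected counts for the whole three-part endpoint.

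**The case against.** The strongest reply is that 30 days is stated three times and the one-week phrase is the outlier. On that view it describes the start of an early look for the DSMB, and site practice may well go further. The DSMB Charter is outside these documents and the participant timeline figure is not shown; either could describe a later check. This stands as a limit on the claim. A reader might infer from protocol 13.7 that later events will go uncounted or be entered as no event, but no section says so. The documents show only that no described procedure would find them.

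A reader might also put a number on the lost events. That needs the share occurring after day 7 and the share treated outside hospital, and the documents give neither.

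A third tempting inference is that key secondary aims 1 and 2 are compromised. Those aims concern severe infections, a term the documents do not define, whereas the SAP component takes any antibiotic-treated infection. It is therefore not shown that missing outpatient infections affects those aims. The SAP plans only to report the proportions and sets no margin, alpha or power for them.

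Nor is there support for bias towards the experimental arm. One check is described for all biopsied men, and equal loss shrinks the absolute difference, which works against the hypothesis of fewer infections.

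None of this removes the contradiction. The sentence that prescribes the work falls short of the endpoint that depends on it.

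**Conclusion.** The inconsistency is real and sits in current text. Protocol 13.7 contradicts its own 30-day commitment, protocol 13.6 and the SAP. As written, 23 of the 30 days and two of the three components lack a described means of ascertainment, so the reported safety proportions could be too low in both arms.

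The conclusion assumes that no procedure outside these documents fills the gap. The number of events missed is unknown. With roughly 11–23 severe infections expected in the whole trial on the plan's own inputs (6.8 + 4.6 to 13.6 + 9.2), even a few missed events would be a visible share.

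The effect is confined to a descriptive secondary safety endpoint and to what the DSMB sees. Cancer detection, biopsy and MRI endpoints are not affected. It should be corrected, but it does not threaten the primary conclusion.

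**What to change.** Reconcile protocol 13.6 and 13.7 with the SAP endpoint table and the SAP follow-up statement:

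1. Keep the early check that starts when results are registered, so that the DSMB still receives early information.
2. Add a record check at or after day 30 for every biopsied man, covering days 0–30 and all three components, done identically in both arms. For men already biopsied this can be done retrospectively.
3. Name the data source for each component, including deaths and antibiotic treatment outside hospital.
4. If the records cannot show outpatient antibiotic treatment, or do not cover all hospitals, state before database lock that the component is incompletely ascertained. Report hospitalisation, infection and death separately. Do not narrow the infection component to hospital-treated cases, because it would then largely duplicate hospitalisation.

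The cost is a small amount of additional record review by the same nurse. A further source for outpatient prescriptions or deaths would add to that, but step 4 gives a transparent course if none is available.

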### ***13.8. Participant timeline***

[figure not shown]

### 13.9. Sample size

Sample size calculations are described in the Statistical Analysis Plan (SAP).

### 13.10. Recruitment and Process Description

The STHLM3-MR Phase 2 will use existing solutions developed and optimized in the previous studies STHLM3 and STHLM3-MR Phase 1 where all major components of the process have been tested.

Figure 2: STHLM3 MR Phase II: Overall design and main process steps. First, participants will follow the *paired design study process* where inclusion, blood-test and delivery of recommendation letter is performed. Men with increased risk of high-grade prostate cancer then enter the *randomized study process*, where extended work-up including biopsies are performed.

[figure not shown]

#### Study part 1 (All participants): Paired study process

##### Step 1: Selection and Invitation

A potential participant list is created by collecting names and addresses for men between ages 50-74 with a permanent mailing address in Stockholm county. Name and address details of potential participants are bought from an external address source, such as SPAR or InfoTorg.

The address list of potential participants is loaded into STHLM3 Participant Handling Register (Microsoft Dynamics CRM configured for this purpose). For each potential participant a unique study ID is created.

An invitation letter is sent to each potential participant, asking if they are willing to participate in the STHLM3 MR Phase II study. The invitation includes:

1. Invitation letter with brief information about the study, including what the potential participant need to do in order to participate
2. Study information brochure with extensive information on the study
3. List of about 60 laboratories in Stockholm that participate in the study including addresses, opening hours, phone numbers, etc.
4. The proposed participant is directed to the website [medicinskastudier.se](https://medicinskastudier.se) for inclusion. At this website, a secure login using "Mobilt BankID" is used and the participant is included after answering studyrelated questions (family history, previous prostate biopsy and current use of selected medicine (finasterid, avodart, dutasterid, proscar and testosteron)). Informed consent is acquired and a unique Study ID is created.
5. An electronic referral with a unique referral ID (RemissID) is generated and activated for blood sampling at any of the blood-sampling stations.

### ***Step 2: Blood Sampling***

The research participants who choose to join the study visit one of the 60 laboratories that collaborate with STHLM3. For many participants, this means that sampling can be conducted close to home or work.

The lab personnel first check the research participant's identity. This is done in the normal way, i.e. by checking the man's identity card and checking that the photo matches the man. The lab personnel then scan the following information on the combined referral and consent form: RemissID, laboratory analysis code (=code that steers robots and transport routines at the laboratory, barcoded) and Kombika (=code for automatic payment through the health care system, barcoded).

The lab personnel then samples a Stockholm3 test from the participant. This is normal venous blood samples of 12 ml.

The blood tests are then passed through the regular health care logistics to A23 laboratory for analysis. A23 conducts the Stockholm3 analysis and sends the results together with the referral ID (RemissID) to the STHLM3 research group. KUL also sends the combined referral and consent form to the STHLM3 research group.

### ***Step 3: Randomization***

Research participants with a total PSA  $\geq 3$  ng/ml and/or a Stockholm3 risk score  $\geq 11\%$  (see above) will be randomized 2:3 to either the reference arm with traditional, systematic biopsies, or to the experimental arm with MRI followed by targeted biopsies.

##### **Step 5a: Reference arm (Traditional biopsies)**

Men randomized to the reference arm will be referred for systematic biopsies at any of the participating urology centers according to Definition of systematic biopsies

After performed biopsy, men are followed in line with clinical practice.

##### **STEP 5b: Experimental arm (MRI and targeted biopsies)**

Men randomized to the experimental arm will be referred to MRI at S:t Göran Hospital or at Unilabs Globen. Radiology data is transferred in accordance to clinical practice to Karolinska Hospital or Capho St Görans radiology department and evaluated in accordance to PI-RADS v2 by study radiologists. Suspected lesions are marked and the report is transmitted to S:t Görans Hospital.

Men with PI-RADS $\geq 3$  lesions will undergo targeted biopsies followed by systematic biopsies. MRI data is loaded into the local Fusion software by the responsible urologist at the time of the biopsy procedure. All procedures include local anesthetics and antibiotic

prophylaxis as recommended by National Guidelines. Separate referrals for systematic and targeted biopsies are used (see appendix).

Men with no visible PI-RADS $\geq$ 3 lesions will be informed by participating urologist and given instructions for systematic follow-up. This follow-up is recommended to include a renewed MR and a STHLM3 test after 12 months.

## **14. Methods (Data Collection, management, analysis)**

### **14.1. Data collection**

Primary data sources are

- i. clinical variables collected from laboratory referral
- ii. biopsy referrals and reports
- iii. pathology reports
- iv. MRI reports
- v. blood analysis reports

Collection of i. – iv. is performed by study nurses ([name]) on a weekly basis from participating urology sites, participating radiologists. For v., this is digitally transferred from A23 laboratory.

### **14.2. Data management**

Data is collected, entered, coded and stored at Department of Medical Epidemiology and Biostatistics, Karolinska Institutet. Data is entered by Study Nurse using predefined database sheets. This is blinded from study co-investigators and data is stored at the department under supervision by the study database administrator (SDA, [name]). Any extraction of study data is performed by the SDA after approval of PI [name].

